## Abstract

**Background:**

Substance use significantly contributes to disease burden among Australians, with harms exacerbated among Aboriginal and Torres Strait Islander peoples by colonisation-related factors like stigma and trauma. Addressing this gap requires culturally acceptable, valid and reliable screening tools, available in a familiar language to the participant, to identify and provide support for those at-risk. This protocol describes a study aimed at validating a culturally-adapted screening tool — the Alcohol, Smoking and Substance Involvement Screening Test (ASSIST) — into Pitjantjatjara, to detect risk of substance-related harm.

**Methods:**

Recruitment will occur at a variety of Aboriginal health and welfare settings across remote, rural and urban South Australia. Eligible participants (aged 18–65) will be briefed and, upon consent, randomly complete the ASSIST app on an iPad and a semi-structured, yarning-style diagnostic interview (see endnote 1) with a health professional and Pitjantjatjara interpreter. The interview will assess for a range of clinically-defined substance use disorders (based on DSM-5-TR and ICD-11 criteria). All participants will be asked to complete the app a second time (between 7 and 28 days) to assess reliability, while a subset of participants at highest-risk will also undergo specialist evaluation from an independent clinician, as a second check for validity.

**Discussion:**

Valid and reliable assessment tools are essential for detecting risky and harmful substance use. If valid, this app has the potential to contribute to community-led efforts to bridge the health gap by addressing modifiable health risk factors.

**Trial registration:**

ANZCTR: ACTRN12625000413426. Open Science Framework pre-registration: https://doi.org/10.17605/OSF.IO/GNZAY.

**Version control number:**

Protocol version 1.1, June 23, 2025.

## Introduction

1

Alcohol, tobacco and illicit drug use remains an ongoing public health concern in Australia. These substances feature in the top-10 risk factors for preventable disease burden [1]. For Aboriginal and Torres Strait Islander peoples (respectfully termed “Indigenous Australians” herein), mental health and substance use disorders account for nearly 25 % of this burden [2]. Regrettably, a health gap persists between Indigenous and non-Indigenous Australians, with individual ‘health risk factors’ (which includes substance use) accounting for nearly 20 % of this gap [3,4]. Substance use behaviours are modifiable with appropriate support. In the Indigenous Australian context, this requires community-led approaches that nurture cultural identity, cultural participation, and ongoing connection to land, country, community, and language [5].

While many Indigenous Australians maintain good health throughout much of their lives, their average health-adjusted life expectancy is about 8 years shorter than non-Indigenous counterparts [5]. Indigenous Australian communities have been working to reduce the health gap over many years [6]. However, unique inequities experienced by Indigenous Australians, dating back to British colonisation in the 18th century, include stigma, discrimination, racism, and intergenerational trauma. These factors continue to impact on health and livelihood [[7], [8], [9], [10], [11]], and compound susceptibility to harm from problematic substance use. Evidence on alcohol consumption among Indigenous Australians is mixed. Some studies suggest Indigenous Australians may be less likely to consume alcohol compared with non-Indigenous Australians [12,13]. However, recent representative community sample studies have shown rates of alcohol consumption in-line with patterns of consumption among the general population in Australia [14]. Other evidence indicates higher rates of risky consumption among those who do consume alcohol [15]. Additionally, nearly one-in-three (29 %) Indigenous Australians report smoking daily; while more than 25 % report using illicit drugs in the past 12-months, predominantly cannabis [16]. Reducing overall risky and harmful substance use requires a tailored public health approach to address health inequities.

Identifying at-risk individuals early allows tailored interventions to reduce substance use escalation and related harms [17]. However, effective secondary prevention strategies, such as screening brief intervention and referral to treatment (SBIRT), rely on accurate and culturally sensitive assessment tools [18,19]. Many existing tools lack sensitivity for use in Indigenous Australian contexts. This is primarily due to language barriers, literacy issues, cultural nuances, and differing worldviews [20,21]. Until recently, few tools were available in language to detect risky substance use, beyond alcohol and tobacco [13,22]. In 2021 some of the authors of this protocol were involved in a community-led project to translate and culturally adapt one such instrument, the Alcohol, Smoking and Substance Involvement Screening Test (ASSIST) [23] into Pitjantjatjara for use in Indigenous Australian communities [24]. The ASSIST was selected for its intent as a secondary preventive approach that screens for all substances and connects that risk assessment to a purpose-built brief intervention.

Recognising the need for cultural adaptation beyond a simple translation, the Pitjantjatjara ASSIST has undergone modifications to enhance its appropriateness for use in Indigenous Australian settings. These include refining language, modifying the structure of some individual the items, and adding audio components in Pitjantjatjara or English to aide comprehension, along with visual elements, including graphics designed by an Aboriginal Australian artist. Given these modifications, validating the ASSIST's reliability and accuracy for detecting risky and harmful substance use is essential. This protocol outlines an order-randomised crossover validation study aimed at assessing the diagnostic accuracy, psychometric performance, and cultural acceptability of the newly developed digital instrument among a sample of Pitjantjatjara-speaking Indigenous Australians, using a gold-standard clinical interview.

## Methods

2

### Indigenous Australian leadership

2.1

The entire project, including the translation and cultural adaptation of the instrument previously reported on [24], was co-designed with Indigenous Australian health professionals (MT, SW), Indigenous Australian researchers (DB) and non-Indigenous Australian researchers (RA, MS, SB, CH, KL, JM, MP). The tablet-based app will be implemented by both Indigenous and non-Indigenous Australian stakeholders. The culturally adapted intervention (currently under development) will be co-designed with stakeholders including Indigenous Australian health professionals, addiction medicine specialists, community leaders, and researchers (Indigenous and non-Indigenous Australian).

### Participants and study design

2.2

The target population for this study are Pitjantjatjara-speaking adult men and women who use alcohol, tobacco or other drugs. We will recruit participants with the full spectrum of substance use behaviours, including those who are abstaining, those who are using recreationally, through to those who are clinically dependent. The purpose of doing so is to identify whether the instrument is capable of differentiating between risk severity among the target group.

#### Inclusion and exclusion criteria

2.2.1

Eligible participants must self-identify as Pitjantjatjara- or English-speaking Anangu (meaning ‘people’ in Pitjantjatjara-Yankunytjatjara, the Traditional Owners of the APY-lands across South Australia, Northern Territory, and Western Australia) and be aged 18–65. Since participants are also required to conduct a diagnostic interview (which will be conducted in English with the aid of a translator), fluency in either (spoken or written) English or Pitjantjatjara is required. Participants who appear intoxicated at the time of the interview will not be eligible to participate in the study, but will still be able to try out app should they choose. All participants will be reimbursed for their time with store vouchers for local grocery stores (e.g., Coles, Woolworths or Foodland/IGA; depending on site) of up-to $90 total value ($30 for completing the ASSIST, $30 for the interview, and a final $30 for completing the follow-up). Grocery store vouchers were selected in this case because, by their nature, cannot be redeemed for alcohol or tobacco or other substances, aligning with ethical considerations for substance use research, and community preferences identified during community consultation.

#### Recruitment

2.2.2

A stratified sampling strategy will be employed to target individuals across the spectrum of risk for each of the five substances included in the Pitjantjatjara ASSIST (“*the app*”, i.e., alcohol, tobacco, cannabis, methamphetamine and inhalants). Since *the app* focuses on these five substances only, and uses existing WHO-ASSIST 3.1 cut-off scores to determine three corresponding levels of risk for each (i.e., low, moderate or high), there are a total of 15 (5x3) possible substance/risk combinations. We will aim to recruit a minimum of 40 individuals to satisfy each of those outcomes (e.g., 40 participants each for low, moderate and high-risk, for each of the substances This could require up to 600 participants, though the total will likely be lower since many use multiple substances. Recruitment will occur until we meet the minimum number for each group, or until the investigators deem it unnecessary to continue. Further details related to the power calculations is found in section 3.5. *Sample Size and Power Calculations* below.

To capture a broad range of participants, we will recruit from a variety of health and welfare settings. The goal is to recruit individuals who are likely to be engaged in low and/or moderate risk alcohol, tobacco or other drug use (e.g., from general health and welfare settings), and those who are more likely to be engaged in use which places them at higher-risk of dependence (e.g., from withdrawal services or other inpatient/outpatient treatment settings). Recruitment will occur at seven different sites across South Australia, by word-of-mouth at each service or setting, where Aboriginal health workers will approach potential participants directly.

#### Sites

2.2.3

Several sites across South Australia are proposed for recruitment. These include the withdrawal service at Drug and Alcohol Services South Australia (DASSA), and the managed alcohol program at DASSA's Glenside Service; Flinders Wellbeing Centre (Salisbury, South Australia); and sites managed by The Aboriginal Drug and Alcohol Council (ADAC; Ceduna, South Australia). Participants may also be recruited from DASSA's Assertive Outreach Program that occurs at various sites within the APY-lands.

#### Procedure

2.2.4

Eligible participants will be approached by an Aboriginal health and welfare worker (“health worker”) at one of the recruitment sites. In most cases, the health worker will be known to the participant, and so an independent research assistant (“independent researcher”) will be introduced to potential participants. For cultural reasons, the health worker and independent researcher will be the same gender as the participants. Prospective participants will be informed by the independent researcher of the study's aims, their right to choose whether or not to participate voluntarily; their right to withdraw at any time should they wish to proceed; and that any refusal will not impact on care they receive from staff at each service (consenting and non-consenting participants will receive the same care as usual from the services they attend). Participants may receive standard care from recruitment sites alongside study interventions, which may be stopped if they request withdrawal or show significant distress, as determined by the research team. No ancillary studies are planned; thus, no additional consent provisions are required.

The independent researcher will also be fluent in Pitjantjatjara, and so will also act as an interpreter/translator to provide additional information or context to participants. The iPad tablet contains both *the app* and the interview. Both components contain the embedded information sheet at the front-end, which participants must read entirely before being allowed to provide consent. Those who agree to proceed will then be randomly allocated to one of two groups, app or interview (using a random sequence generator built onto the iPad). The individual initiates the randomisation sequence, which conceals allocation sequencing until assignment.

Once informed consent has been given via the iPad, participants randomised to *the app*-first group will be given a guided visual and tactile demonstration of how to use *the app* by a member of the research team (either health worker or interpreter) and then be asked to complete the instrument on their own. The research team members will sit a short distance away in case there are questions or technical issues with *the app*. Participants will then be provided with a $30 voucher and given a short break before completing the interview.

Participants randomised to the interview-first condition will sit down with the independent researcher/interpreter to conduct the yarning-style interview. At the outset, participants will be asked the same four initial anonymous identifier questions for the purposes of matching data from the interview and app. All interviews will be conducted face-to-face. All data will be recoded in REDCap. Participants will receive $30 voucher for completing the interview. Participants will then be given a short break before completing *the app*.

Upon completion, a follow-up appointment will be scheduled with participants for within fourteen days. At follow-up participants will also be asked to complete *the app* assessment component again (i.e., but not the interview), in order to assess *the app*'s test-retest reliability. To maximise follow-up retention, participants will receive a final $30 voucher, but only upon completion of the final assessment.

For participants taking part in the DASSA withdrawal service (i.e., those representing a higher risk group), an independent clinical assessment, conducted by an Addiction Medicine Registrar employed at the service, will also be used as an additional check of validity. The independent assessment form will include the same unique participant code (see preceding *2.3.1. Unique participant code* section), as well as participants’ age and gender. The assessment will be recorded on a digital form in REDCap and will be completed by the doctor at the service.

#### Adverse events

2.2.5

In the event that participants experience distress, a research team member will be available to provide immediate assistance and facilitate access to support services. Should participants express personal concerns or exhibit signs of distress, prompt support will be provided. If a participant wishes to withdraw from the study, we will help them contact their healthcare provider or access immediate care. Emergency services and mental health triage contact information are included in the Pitjantjatjara ASSIST app, which also offers a directory of support services, enabling participants to access relevant phone numbers or websites.

### Data collection and instruments

2.3

#### Unique participant code

2.3.1

Given there are multiple stages of this study (*the app* assessment, diagnostic interview (with independent evaluation for the high-risk group), and follow-up *app* assessment), it is necessary for the researchers to match participants responses through each stage. Since *the app* and diagnostic interview refer to sensitive information, it is also necessary to avoid capturing participant information that could be used to identify them. To mitigate the risk of sensitive information becoming identifiable, a unique participant code that anonymises the participant and their data to everyone, including the research team will be created automatically during both the app and interview stages.

The unique code will be generated automatically by the participant, based on their answers to the following four questions: what is your birth month? (coded 0–12); what is the first letter of your mother's first name? (coded A-Z); how many children do you have? (coded 0–99), and; what is the first letter of your first name? (coded A-Z). Participants will provide responses to these four questions anonymously within *the app*, or interview at the consenting stage, and the participant's unique combination of integers and digits will be concatenated to form each participant's unique code. So, for example, a person born in August (08), who's mother's name was Jenny (J), with three children (3), and who's own name was Mark(M), would be 08J3M. Structured in this way, anonymous data will be stored for each participant, preventing any risk of identification. Unique codes will be generated and stored automatically in the REDCap database.

#### Pitjantjatjara ASSIST

2.3.2

The Pitjantjatjara ASSIST is a translated and culturally-adapted version of the ASSIST (ref for original ASSIST). Like the full ASSIST, the Pitjantjatjara ASSIST is an 8-item questionnaire designed to assess risk of harm from substance use disorders. However, unlike the full ASSIST, the adapted instrument only focuses on five primary drugs of concern in the Pitjantjatjara community, which include alcohol, tobacco, cannabis (“marijuana”), methamphetamine (“ice”), and inhalants. Additionally, unlike the full ASSIST, the adapted instrument steps *the app*-user through items 2–7 for each substance sequentially. The scoring algorithm for the adapted instrument remains unchanged. Upon completion of the instrument, individual's substance-specific scores for each inventory (SSI) will be summed, and presented with a corresponding calculation of risk. The English version of the ASSIST has been validated in a variety of health and welfare settings and populations [25]. A detailed description of the app, including design, flow, and features is available as an appendix (see supplementary materials).

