#### Diagnostic interview

2.3.3

To validate *the app* against a clinical gold-standard for diagnosing DSM-5 [26] and ICD-11 [27] substance-related disorders; a diagnostic interview will also be conducted with each participant, on the same day as they complete the ASSIST app. The interview is based on the DIS-SAM [28], which has been modified to identify the presence or absence of clinical symptoms for ICD-11 (for hazardous use, harmful use, and dependence) and DSM-5-TR substance use disorder, and includes assessments at both the past 12-month, and past 3-month intervals.

The interview will be conducted by either a male or female health professional (matched to participant's gender). The health professional will understand Pitjantjatjara culture and context but may not be Aboriginal or fluent in the language. Therefore, in addition, an Aboriginal man or woman will also be present at all times to aid interpretation of questions. The choice to include both Aboriginal and non-Indigenous Australian healthcare workers was taken to mitigate the risk that the differences in culture will impact the quality of the assessment [20,21,29]. Interviewers assessments will be based on use in the past 90, and 365 days.

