#### Independent clinical evaluation

2.3.4

Participants recruited from the DASSA withdrawal service will also undergo an independent clinical evaluation from an addiction medicine specialist, trained to diagnose the presence or absence of ICD-11 and DSM-5-TR disorders related to substance use. The registrar will be blinded from the outcome of the earlier assessment and will provide a clinical opinion as to whether the individual in their care meets the diagnostic threshold for hazardous use, harmful use or dependence (ICD-11) and substance use disorder (DSM-5-TR) for each of the five substances. In all cases, the individual will be known to the clinician (as a patient of the service).

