#### Concurrent validity

3.2.1

Concurrent validity will be assessed in two ways. First, a confirmatory approach will assess the partial-order (Spearman's Rho [ρ]) correlation between ASSIST SSI scores for each scale, and the total number of DSM-5-TR and ICD-11 diagnostic symptoms reported for that substance. The use of partial correlations will help to control for the effects of other substances and demographic factors. Benjamini-Hochberg (BH) correction will be used for each correlation to control the False Discovery Rate (FDR) [41]. BH-corrected significant (FDR <0.05) partial correlation ρ ≥ 0.5 will indicate concurrent validity.

The second (exploratory) approach will involve assessing the relationship between ASSIST SSI scores and the number of DSM-5-TR/ICD-11 symptoms through linear and quadratic regression models. For every substance, a regression plot will map the number of ICD-11/DSM-5-TR symptoms reported (vertically along the y-axis) as a function of the ASSIST SSI score (horizontally on the x-axis). As there are five substances, and two distinct classification systems, a total of 20 separate regression models will be carried out (10 linear, and 10 quadratic). For each substance, a significant linear and/or quadratic relationship (*p* < 0.05) is expected to be found between the number of symptoms reported and the average ASSIST scores. Model fit indices will be reported, and models will be compared using AIC and BIC values, to prevent overfitting. Models with the lowest AIC/BIC values will be selected.

A final check for concurrent validity (depending on sufficient data) will investigate the relationship between ASSIST SSI scores for each substance, and the outcomes from the independent clinical assessment by an Addiction Medicine Specialist. For each substance, a logistic regression model will be used to assess the probability of reaching a diagnosis, per unit score increase on the ASSIST. For each substance, a significant model (*p* < 0.05) is expected to be found between the ASSIST scores and the diagnosis probability.

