## Discussion

4

The Pitjantjatjara ASSIST has been transformed across a number of dimensions to increase its cultural appropriateness. The next step is to assess its validity, reliability and acceptability for use with Indigenous Australian populations. Given the lack of valid, culturally appropriate and reliable instruments for detecting risky substance use, validation of *the app* adds to the growing list of community-driven initiatives aimed at closing the health gap in Australia.

A valid, reliable app detecting risky substance use in Indigenous Australian settings could reduce such use population-wide. In addition, an instrument with a high degree of diagnostic accuracy may be able to provide a greater degree of insight into the prevalence of substance use disorders (including dependence) within the Indigenous Australian population. Assuming *the app* is valid and reliable, future research will also focus on identifying the rate of substance use disorders among the Indigenous Australian community.

While there are a number of strengths of this research, there are also some potential limitations that need to be discussed. Primarily, *the app* relies on accurate self-report data, which can be a challenge in Indigenous Australian settings for a number of reasons, including stigma, shame, cultural sensitivity, and general distrust that occurs around disclosure of substance use [20,21]. *The app* used here however, is designed to address some of these challenges, by prioritising capacity for anonymous, self-assessment and feedback. Additionally, as the app is currently only in Pitjantjatjara and English, it excludes many Indigenous Australians not fluent or literate in these languages. Therefore future research will also be needed to investigate the validity and reliability of both the English version of *the app*, as well as any additional languages that are developed and added in the future.

This project acknowledges the unique challenges and strengths that Indigenous Australian communities face in addressing the harm from substance use disorders. The Pitjantjatjara ASSIST — developed largely by, and with community — serves as a reminder about the role that community should play in the development, implementation and scale-up of culturally-grounded public health strategies.

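### As written, app-first participants can see their risk result before the same-day reference interview, and no blinding is stated for that interview, so the app can influence the standard it is judged against

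*Protocol article*

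**What the plan says.** - **Result display.** Section 2.3.2 (Pitjantjatjara ASSIST) says that when the instrument is finished, "individual's substance-specific scores for each inventory (SSI) will be summed, and presented with a corresponding calculation of risk". The sentence does not name the viewer. The Discussion describes the app as "prioritising capacity for anonymous, self-assessment and feedback", which points to the participant.
- **Order.** Section 2.2.4 (Procedure): "Those who agree to proceed will then be randomly allocated to one of two groups, app or interview". The allocation ratio is not given. The Introduction calls the study an order-randomised crossover.
- **App-first sequence.** Section 2.2.4: "Participants will then be provided with a $30 voucher and given a short break before completing the interview". Section 2.3.3 places the interview "on the same day as they complete the ASSIST app".
- **Staff.** The health worker or interpreter demonstrates the app beforehand. Team members stay nearby while the participant completes it alone. The independent researcher, who is also the interpreter, takes part in the interview.
- **Blinding.** Section 2.3.4 (Independent clinical evaluation): "The registrar will be blinded from the outcome of the earlier assessment". This is the article's only blinding statement, and it covers only withdrawal-service participants.
- **Analysis.** For the confirmatory correlations, section 3.2.1 says: "The use of partial correlations will help to control for the effects of other substances and demographic factors". Sections 3.1 to 3.5 do not mention order. A detailed SAP and a description of the app's flow are said to be in appendices, which are not shown.

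**The concern.** In an accuracy study the reference standard should be set without knowledge of the index test. Here the sequence allows a participant to be told a low, moderate or high risk level for each substance and then, after a short pause, to be interviewed about symptoms for the same substances. The Discussion itself notes that stigma, shame and distrust affect disclosure, so interview answers could plausibly respond to what the screen has just shown.

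Two features raise the stakes. First, success is judged against fixed marks (AUC at least 0.71 in section 3.3.1, partial correlation at least 0.5 in section 3.2.1), so a modest shift can decide the conclusion when the true value lies near a mark. Second, the displayed level uses the existing WHO cut-offs (section 2.2.2), while section 3.3 derives new cut-offs from the same interviews. If answers drift toward the displayed category, the new cut-offs may be drawn toward the old ones.

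**Working it through.** The plan states no figure for this effect, so there is nothing to reproduce. The check has three parts.

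**1. Does the sequence allow it?** Section 2.3.2 shows the result on completion. Sections 2.2.4 and 2.3.3 put the interview after a short break on the same day. No section makes an exception for app-first participants. Section 2.3.4 blinds the registrar and nobody else is mentioned. Followed as written, the index result can reach the participant, and possibly the interpreter, before the reference diagnosis is fixed.

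**2. How large could it be?** Inputs:

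- Sensitivity 0.70: the planning value in section 3.5, given there for the independent-assessment model and borrowed here.
- Specificity 0.70 and 1:1 order allocation: assumed.
- Prevalence 50%: assumed, in line with the 1:1 case ratio that section 3.5 aims for.
- Carry-over c, the fraction of discordant interview calls in the app-first share s that move to the app result: assumed, 10% to 50%.

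The starting proportions are TP = TN = 0.35 and FP = FN = 0.15. The interview call is what changes, so false negatives become true negatives and false positives become true positives, and the denominators move too. With k = s × c:

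TP' = TP + k·FP; FN' = FN·(1 − k); TN' = TN + k·FN; FP' = FP·(1 − k)

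At 50% prevalence with equal sensitivity and specificity, all margins stay at 0.5. Chance agreement is therefore 0.5, and the simple two-by-two kappa is (agreement − 0.5)/0.5.

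| c | k (s = 0.5) | TP' | FN' | Sensitivity = specificity | Kappa |
|---|---|---|---|---|---|
| 0 | 0 | 0.350 | 0.150 | 0.700 | 0.40 |
| 10% | 0.05 | 0.3575 | 0.1425 | 0.715 | 0.43 |
| 25% | 0.125 | 0.36875 | 0.13125 | 0.7375 | 0.475 |
| 50% | 0.25 | 0.3875 | 0.1125 | 0.775 | 0.55 |

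With an app-first share of 40% to 60% and c = 25%, sensitivity is 0.730 to 0.745.

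Prevalence also matters. At 20% prevalence, s = 0.5 and c = 25%:

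- TP' = 0.14 + 0.125 × 0.24 = 0.17 and FN' = 0.06 × 0.875 = 0.0525, so sensitivity is 0.17/0.2225 = 0.764.
- TN' = 0.56 + 0.125 × 0.06 = 0.5675 and FP' = 0.24 × 0.875 = 0.21, so specificity is 0.5675/0.7775 = 0.730.

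The direction can reverse. Return to 50% prevalence and suppose that 10% of app-first true positives, having seen their result, deny symptoms at interview. Then 0.5 × 0.10 × 0.35 = 0.0175 moves from TP to FP. Sensitivity becomes 0.3325/0.4825 = 0.689 and specificity 0.35/0.5175 = 0.676.

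**3. Could a comparison by order detect it?** Section 2.2.2 aims for at least 40 participants per substance and risk level. Those cells are defined by app risk, so 40 interview-positive cases, 20 per order, is an assumption. The 95% half-width for a difference in sensitivity is 1.96 × √(2 × 0.70 × 0.30/20) = 0.28. Power to distinguish 0.70 from 0.85 is about 20%.

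**The case against.** The strongest reply is that this is a condensed article. The app's flow sits in an unshown appendix, which might show that the study version hides the result between components. The SAP might contain an analysis by order. Section 3.2.1 does not present its adjustment set as complete. The order-analysis point therefore cannot be called an omission and is only secondary here. The sequence and the single blinding statement, however, are fixed in the article itself, and a SAP cannot undo a result already shown.

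A reader might also infer more than the documents support:

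- **That interviewers are unblinded.** They are not said to receive app output. Participants complete the app alone with staff at a distance, any demonstration comes before completion, and data are held under an anonymous code. What is missing is a statement, and the route through the participant stays open.
- **That the interview diagnosis is discretionary.** The discretion in section 2.3.3 covers metaphors, examples and explanations. A checklist ties topics to diagnostic criteria.
- **That half the sample is affected and agreement is inflated.** The 1:1 split is not stated, influence is possible rather than shown, and a participant shown a high-risk result might minimise.
- **That the interview-first group is a clean benchmark.** It is free of app feedback, but the interview may influence the later app answers.

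**Conclusion.** The concern holds as a design weakness. As written, the index result can be known to the participant before the reference standard is set, and the main interview has no stated safeguard. The resulting bias in sensitivity, specificity, AUC, kappa and the correlations is possible, most plausibly toward agreement, but neither its presence nor its direction is certain. Randomised order makes the effect open to inspection but does not remove it from pooled estimates.

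The illustrated rise of 1.5 to 7.5 points in pooled sensitivity (0.03 to 0.15 in kappa) rests entirely on the assumed carry-over, accuracy, prevalence and order split. With no carry-over there is no bias. No stated sample size or power figure is affected.

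**What to change.** 1. Hold the app's result screen until both app and interview are complete, then show it at the same visit.
2. State that the interviewer and interpreter do not see app output before the diagnosis form is locked.
3. As a secondary check, unless the SAP already has it, report accuracy and agreement by randomised order as estimates with confidence intervals. Note the low precision (half-width about 0.28 with 20 cases per order), that a non-significant difference would not rule the effect out, and that interview-first participants may carry over from interview to app.

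Adding order as an additive covariate in the partial correlations would not serve. It removes a mean shift between orders, whereas the issue is a change in the app-interview association by order.

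The cost is an app setting, a line or two in the procedure and one extra table. The downside is that app-first participants wait for feedback until after the interview. The sample size does not change.
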